### Objectives

The primary aim of the present study is to determine the effectiveness of a home-based palliative approach (HPA) on MS symptoms and HRQOL of people with severe MS. Secondary outcomes are changes in patient functional status and mood; changes in carer HRQOL, mood and caregiving burden; costs; incorporation with standard care; unplanned hospital admissions; referrals to hospice; and deaths over the six-month intervention.

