#### Secondary outcomes

Secondary outcome measures are HRQOL as assessed by Core-POS [34] and European Quality of Life Five Dimensions (EQ-5D) [37,38]; mood as assessed by the Hospital Anxiety and Depression Scale (HADS) [39,40]; impairment/activity limitations as assessed by EDSS [19] and Functional Independence Measure (FIM) [41,42]; and direct and indirect tangible costs are assessed by the MS foundation Costs Questionnaire (MSCQ) [43].

Carer outcomes are: HRQOL as measured by Short Form 36 (SF-36) [44,45] and EQ-5D; mood as measured by the HADS; and carer burden as measured by the Zarit Burden Interview (ZBI) [46,47].

Recruitment rates, reasons for exclusion, time to delivery of interventions, adherence to intervention (see the HPA group), protocol deviations, incorporation with standard care, unplanned hospital admissions, referrals to hospice, deaths (place and cause) are also considered over the six-month period.

Outcome assessments (Table 2) are carried out at baseline, and after three and six months, by a blind examiner at the patient’s home. In addition, six telephone interviews are performed, on a monthly basis, by a trained interviewer who administers the full MSCQ (at three and six months) and pertinent MSCQ sections (at one, two, four and five months).

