#### Statistical analyses

Continuous data will be summarized using means, medians, SDs, minimums and maximums. Between-group comparisons will employ either the two-sided unpaired *t* test or Wilcoxon’s two-sided two-sample test for non-normal data. Distributions will be tested for normality using the Shapiro-Wilk test. Correlations will be estimated using Spearman’s or Pearson’s coefficients. Categorical data will be compared by χ2 or Fisher’s exact test.

Longitudinal changes in SEIQoL-DW and POS-S-MS will be analyzed using linear mixed models for longitudinal data [48,49]. All tests will be two-tailed. *P* values <0.05 will be considered significant. For the primary intention-to-treat analyses, multiple imputation of missing values will employ Rubin’s approach. The analyses will be performed with Stata Statistical Software, release 12 (StataCorp LP, College Station, TX, USA), or SAS, release 9.2 (SAS Institute Inc., Cary, NC, USA).

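### A Shapiro-Wilk gate between t test and Wilcoxon, with no exemption for costs, would send skewed costs to a rank test that does not address the difference in mean cost

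*Protocol article*

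**What the plan says.** The Statistical analyses section of the protocol article sets one general scheme. For description, "Continuous data will be summarized using means, medians, SDs, minimums and maximums". For between-group comparison it gives the two-sided unpaired t test or Wilcoxon's "two-sided two-sample test for non-normal data". The choice rests on a pre-test: "Distributions will be tested for normality using the Shapiro-Wilk test". The level of that pre-test, and whether it is applied per arm or to pooled data, is not given. "All tests will be two-tailed", and the significance threshold is 0.05.

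One pair of outcomes has its own method: "Longitudinal changes in SEIQoL-DW and POS-S-MS will be analyzed using linear mixed models for longitudinal data".

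Costs appear in Objectives among the secondary outcomes, and Secondary outcomes says that "direct and indirect tangible costs are assessed by the MS foundation Costs Questionnaire". No separate method for costs is named, and nothing takes them out of the general scheme.

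**The concern.** Costs of care usually have a long upper tail. If they do here, Shapiro-Wilk will reject normality and the written scheme leads to Wilcoxon. That test asks whether costs in one arm tend to exceed those in the other. It does not compare arithmetic means, and the mean, multiplied by the number of dyads, is what gives total spending. The two questions can have different answers. An intervention that raises the typical cost a little and removes some very expensive cases can leave the mean unchanged and still give a small Wilcoxon P value. The reverse can also happen: a real difference in mean cost with no shift in ranks.

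At stake is how one secondary outcome is read. A mean-neutral HPA could be reported as significantly different in cost, or a real difference in mean cost could be missed. For the secondary scale scores the issue is smaller: the reported contrast could change from a mean difference to a rank comparison between outcomes or between the three- and six-month visits.

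**Working it through.** **Plan's own figures.** The article gives no figure for costs or for the behaviour of the pre-test rule. Its only related figures are the t-test powers in Sample size. With SE = √(s₁²/n₁ + s₂²/n₂), the Welch degrees of freedom and the noncentral t distribution:

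- POS-S-MS: difference 0.2 − (−0.4) = 0.6; SE = √(0.5²/41 + 0.8²/21) = 0.191; power 85.7% (stated 85%).
- SEIQoL-DW: difference 31.5 − 12.1 = 19.4; SE = √(12.8²/21 + 19.3²/11) = 6.45; power 80.1% (stated 80%).

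Both reproduce. They do not bear on costs.

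**Inputs.** From the article: 50 HPA and 25 UC planned, 41 and 21 as the evaluable POS-S-MS numbers, two-sided 0.05. Assumed, because the article gives no cost distribution: lognormal costs with the same mean in both arms, and log-SDs from 0.5 to 1.2. Also assumed: Shapiro-Wilk at 0.05 in each arm, Wilcoxon if either arm rejects, otherwise the t test.

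**Equal means.** A lognormal cost has mean exp(μ + s²/2). Setting μ = −s²/2 in each arm makes both means 1. Then

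- median HPA / median UC = exp(δ), with δ = (s_UC² − s_HPA²)/2;
- P(HPA cost > UC cost) = Φ(δ / √(s_HPA² + s_UC²)).

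For 0.7/1.2: δ = (1.44 − 0.49)/2 = 0.475; median ratio exp(0.475) = 1.61; probability Φ(0.475/1.389) = 0.63. The other rows follow in the same way.

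**Step 1: which test is selected?** With log-SD 0.5 in both arms, at least one arm rejected normality in 97% of trials at 50/25 and 93% at 41/21. In the more skewed settings it was essentially 100%. So the rule almost always selects Wilcoxon.

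**Step 2: what does the rule report when mean costs are equal?** About 4,000 simulated trials per setting at 50/25:

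| log-SD HPA/UC | median ratio | P(HPA > UC) | rule gives P<0.05 |
|---|---|---|---|
| 1.0/1.0 | 1.00 | 0.50 | about 4–5% |
| 0.8/1.0 | 1.20 | 0.56 | 13% |
| 0.8/1.2 | 1.49 | 0.61 | 35% |
| 0.7/1.2 | 1.61 | 0.63 | 47% |

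The simulation standard error at 47% is √(0.47 × 0.53 / 4000) = 0.8 percentage points. Reversing the last row (HPA 1.2, UC 0.7) also gives 47%. At 41/21 the rule gave 4.3% for 1.0/1.0 and 12% to 60% across the unequal shapes tried.

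**Step 3: the converse.** With equal medians and log-SD 0.7/1.2, the ratio of means is exp((0.49 − 1.44)/2) = 0.62. Wilcoxon gave P<0.05 in only 7.6% of trials.

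**Step 4: do comparisons of means do better?** With equal means at 50/25, Welch rejected in 5.0% (1.0/1.0), 7.2% (0.8/1.0) and 12.3% (0.7/1.2), but 5.0% when the larger arm had the wider spread (1.2/0.7). A within-arm percentile bootstrap rejected in about 8% (1.0/1.0) and about 13% (0.7/1.2), with differences of a point or so between runs.

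**Step 5: normally distributed scale scores.** At 40/20, an either-arm Shapiro-Wilk sends about 10% of truly normal outcomes to Wilcoxon. The type I error of the complete two-stage rule is 5.1%.

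**The case against.** The case on the other side is substantial, and most of it narrows the point.

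- **The primary outcomes are outside the rule.** A reader might infer that every continuous outcome depends on the pre-test. The article does not support that: the longitudinal analyses of SEIQoL-DW and POS-S-MS are assigned to mixed models. This stands.
- **The mean-cost target is not in the article.** It lists costs and says how they are measured; it states no mean-cost estimand and no cost-effectiveness or budget question. The arithmetic mean is the usual target but is an assumption here. The plan would also report mean costs descriptively, so what is lacking is inference on the mean. This stands.
- **The article does not assign costs to Wilcoxon by name.** They fall under the general scheme because nothing exempts them, and a separate economic plan may exist. The possibility stands, but such a plan would have to override a stated rule and not merely fill a gap.
- **47% might be read as Wilcoxon's false-positive rate.** It is not. In that setting the distributions really differ: the HPA median is 1.61 times the UC median, and the UC cost SD is about 2.3 times the HPA SD (√(e^1.44 − 1) / √(e^0.49 − 1) = 1.79/0.80). Wilcoxon answers its own question correctly. When the shapes are the same, the rule holds about 5%.
- **One might infer that the pre-test damages the scale scores.** For normal data the two-stage error is 5.1%, so no such harm is shown.
- **The replacement is imperfect.** With the same shape in both arms, the percentile bootstrap (about 8%) does worse than the planned rule. This stands and has to be stated with the fix.

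**Conclusion.** The point holds as a limited one about a secondary outcome. As written, the general rule covers costs, and with even mild right skew it almost always leads to Wilcoxon, which does not test a difference in mean cost. How far that misleads depends on how much the shape of the cost distribution differs between arms: no excess with identical shapes, 13% at 0.8/1.0, and 35% to 47% in the more divergent settings, all with equal true means. These figures rest on assumed lognormal costs, an assumed 0.05 either-arm pre-test and an assumed mean-cost question. They show what can happen and do not forecast this trial. The primary mixed-model analyses are untouched. For the secondary scale scores the case for change is consistency of the reported contrast, not error control. It is a desirable improvement, not an essential one.

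**What to change.** For costs, remove the Shapiro-Wilk gate and name the method in advance: the difference in arithmetic mean cost between arms, with a confidence interval from an unequal-variance method or from a bootstrap resampled within arm. Keep Wilcoxon as a sensitivity analysis, labelled as a comparison of distributions. State that the mean difference is the target, or, if another target is intended, say which.

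For the secondary scale scores, fix one method per outcome so that the same contrast is reported at three and six months.

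The cost is a few sentences of analysis wording; no data or participants are added. The downside is precision and coverage. With 25 UC dyads the mean-cost intervals will be wide and only approximate: with equal means, simulated rejection was about 5% to 12% for Welch and about 8% to 13% for the percentile bootstrap. The report should say so.

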#### Randomization

Eligible study participants are randomized to either HPA or UC using third-party, web-based computerized randomization software. A stratified minimization algorithm is used to ensure balance of possible prognostic factors across the two groups (EDSS (8.0 to 8.5, 9.0 to 9.5), presence of severe cognitive compromise (clinical judgment), and center (Milan, Rome, Catania)). Following randomization, an email informing on dyad assignment is sent to the PI and the HPA team. The team informs the dyad about assignment. The team also contacts the patient’s caring physician (GP, neurologist or other physician responsible for the patient’s care) to inform him/her about the study and (for dyads assigned to HPA) define a common agenda.

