**Table 2 Tab2:** **Outcome measures and timing of follow-up**

	**Baseline**	**Three-month follow-up**	**Six-month follow-up**
General characteristics	X	X	X
MS history	X	X	X
Medical history	X	X	X
EDSS	X	X	X
FIM	X	X	X
SEIQoL-DW^*^	X	X	X
Core-POS^**^	X	X	X
POS-S-MS^**^	X	X	X
HADS^*^	X	X	X
EQ-5D^*^	X	X	X
MSCQ	X	†	†
Carer characteristics /medical history	X	X	X
Carer HADS	X	X	X
Carer SF-36	X	X	X
Carer EQ-5D	X	X	X
Carer ZBI	X	X	X

To preserve blinding, all outcome measures (except MSCQ) are assessed during examiner visits at three and six months follow-up. ^*^Not assessed in MS patients with severe cognitive compromise or unable to communicate; ^**^carer versions used in MS patients with severe cognitive compromise or unable to communicate; ^†^assessed by phone interview. Core-POS, Core-Palliative care Outcome Scale; EDSS, Expanded Disability Status Scale; EQ-5D, European Quality of Life Five Dimensions; FIM, Functional Independence Measure; HADS, Hospital Anxiety and Depression Scale; MSCQ, Multiple Sclerosis foundation Costs Questionnaire; MS, multiple sclerosis; POS-S-MS, Palliative care Outcome Scale-Symptoms-Multiple Sclerosis; SF-36, Short Form 36; SEIQoL-DW, Schedule for the Evaluation of Individual Quality of Life-Direct Weighting; ZBI, Zarit Burden Interview.

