#### Sample size

The sample size was based on previous data for SEIQoL-DW [15] and POS-S-MS [8]; for both outcomes we considered changes at three months compared to baseline.

SEIQoL-DW: a sample size of 21 patients assigned to HPA (study intervention) and 11 assigned to UC (control) has a power of 80% to detect an assumed mean change of score of 31.5 (standard deviation (SD) 12.8) in the HPA group compared to a change of 12.1 (SD 19.3) (null hypothesis) in the UC group, at alpha level 0.05 using a two-sided, two-sample *t* test. Assuming 20% dropout, 25 patients are required in the HPA group and 13 in the UC group (total sample size 38).

POS-S-MS: a sample size of 41 HPA and 21 UC has a power of 85% to detect an assumed mean change of −0.4 (SD 0.5) in the HPA group, with a concomitant change of 0.2 (SD 0.8) (null hypothesis) in the UC group; assuming an alpha level of 0.05 and a two-sided, two-sample *t* test. Assuming 20% dropout, 49 patients are required in the HPA group and 25 patients in the UC group (total sample size 74).

It is expected that up to 50% of MS patients have severe cognitive compromise, and will not be able to complete SEIQoL-DW, in these the only primary endpoint will be the POS-S-MS. We aim to recruit 50 patients in the HPA group and 25 patients in the UC group, thereby achieving an exact 2:1 ratio of intervention to control.

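### Allocation is minimised on three factors, but the only fully specified tests are unadjusted, and the mixed model is stated without those factors or any handling of baseline

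*Protocol article*

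**What the plan says.** **Allocation.** The Randomization section states that "A stratified minimization algorithm is used to ensure balance of possible prognostic factors across the two groups". The factors are EDSS band (two levels), severe cognitive compromise (yes or no) and center (three).

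**Sizing.** The Sample size section takes change from baseline at three months and powers each primary outcome "at alpha level 0.05 using a two-sided, two-sample" t test. For SEIQoL-DW it uses "an assumed mean change of score of 31.5 (standard deviation (SD) 12.8) in the HPA group"; the UC figure set against it is 12.1, with SD 19.3. No covariate enters either calculation.

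**Analysis.** The Statistical analyses section gives the unpaired t test, or Wilcoxon's two-sample test for non-normal data, for between-group comparisons. On the primary outcomes it adds: "Longitudinal changes in SEIQoL-DW and POS-S-MS will be analyzed using linear mixed models for longitudinal data". It lists no fixed effects, no covariates and no treatment of the baseline score. Multiple imputation is named for the primary intention-to-treat analyses.

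**Who rates.** Under Table 2, patients with severe cognitive compromise or unable to communicate are not assessed on SEIQoL-DW. For POS-S-MS the footnote reads: "carer versions used in MS patients with severe cognitive compromise or unable to communicate".

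**The concern.** Minimisation removes most of the between-arm imbalance in the chosen factors. An unadjusted standard error is computed as if that imbalance could still occur. If the factors predict the outcome, it is therefore too large for the allocation actually used, and the test rejects less often than its nominal 5%.

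A second loss concerns baseline. A plain comparison of changes gives the baseline score a fixed coefficient of one. Estimating that coefficient is at least as precise in large samples, and more precise unless baseline and follow-up are almost perfectly correlated.

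Both losses fall on a trial whose Limitations section calls 75 patients rather small for its phase and gives that as the reason for minimising. SEIQoL-DW has the least to spare, because up to half of the patients are expected to be unable to complete it. Every variable needed for adjustment is already collected at or before the baseline visit.

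**Working it through.** **1. Inputs, all from the Sample size section.** Two-sided alpha is 0.05.
- SEIQoL-DW: 21 HPA and 11 UC; changes 31.5 (SD 12.8) and 12.1 (SD 19.3); difference 19.4; stated power 80%.
- POS-S-MS: 41 HPA and 21 UC; changes −0.4 (SD 0.5) and 0.2 (SD 0.8); difference 0.6; stated power 85%.

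**2. Reproducing the stated power.** I used a two-sample t test with unequal variances, Satterthwaite degrees of freedom and the noncentral t distribution.
- SEIQoL-DW: SE = √(12.8²/21 + 19.3²/11) = √(7.80 + 33.86) = 6.45; df 14.7; 19.4/6.45 = 3.01; power 80.1%.
- POS-S-MS: SE = √(0.5²/41 + 0.8²/21) = √(0.00610 + 0.03048) = 0.191; df 28.2; 0.6/0.191 = 3.14; power 85.7%.

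Both match the article. A pooled-variance t test would give 91.0% and 94.6%, which do not. The stated power thus belongs to an unadjusted change-score test and takes no credit for baseline or the minimisation factors.

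**3. Baseline score.** Let the score have the same variance σ² at baseline and follow-up, with correlation ρ. The change has variance 2σ²(1 − ρ). The follow-up score adjusted for baseline has residual variance σ²(1 − ρ²). The ratio is (1 + ρ)/2, so the SE is multiplied by √((1 + ρ)/2). The article does not give ρ; the values below are assumed.

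| ρ | SE factor | SEIQoL-DW power (from 80.1%) | POS-S-MS power (from 85.7%) |
|---|---|---|---|
| 0.3 | 0.81 | 93.5% | 96.4% |
| 0.5 | 0.87 | 89.9% | 93.8% |
| 0.7 | 0.92 | 86.0% | 90.7% |

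The gain is about 6 to 13 points for SEIQoL-DW and 5 to 11 for POS-S-MS. It goes to nothing as ρ approaches 1.

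**4. Minimisation factors.** Suppose the factors explain a share R² of the outcome variance and balance is near perfect. The unadjusted SE is then too large by 1/√(1 − R²), and the true two-sided size is about 2[1 − Φ(1.96/√(1 − R²))]. R² is also not in the article.

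| R² | Interval too wide by | True size of nominal 5% test |
|---|---|---|
| 0 | 0% | 5% |
| 0.05 | 2.6% | 4.4% |
| 0.10 | 5.4% | 3.9% |
| 0.20 | 11.8% | 2.8% |
| 0.30 | 19.5% | 1.9% |

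**5. Check by simulation.** I simulated biased-coin minimisation (probability 0.9) on 2 × 2 × 3 factors, 2:1, n = 60, with 4,000 trials per setting. At R² of 0.10, 0.20 and 0.30 the unadjusted test rejected in 3.5%, 2.8% and 2.2% of null trials, and the adjusted test in 4.8%, 4.7% and 5.1%. Adjusted-to-unadjusted SE ratios were 0.95, 0.90 and 0.84, as step 4 predicts. In a separate run of 3,000 trials with R² = 0, adjusting for the factors cost about 0.4% in SE. The layout fits POS-S-MS. It does not fit SEIQoL-DW, where cognitive compromise is constant and the sample is about half as large.

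**The case against.** The strongest reply is that the article never says the mixed model is unadjusted. It names a class of model and stops there. A longitudinal mixed model may carry baseline as a response or as a covariate, and a journal article commonly leaves the covariate list to a fuller document. On this view the t and Wilcoxon sentence is generic text about continuous data, and the t test under Sample size is only a planning device. This stands as a limit: a reader might infer a mixed model fitted without the minimisation factors or baseline, but the text leaves that open. It does not remove the point. The only between-group tests that are fully specified cannot take covariates, the sizing uses the same kind of test, and nothing in the article brings these variables into any analysis.

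Four further limits also stand.
- The article calls the factors only possibly prognostic. If the response is change, any stable effect of a factor on the level of the score cancels, so the upper R² values are not to be expected without evidence.
- Severe cognitive compromise is constant for SEIQoL-DW. Only EDSS band and center can matter there.
- One ρ for both arms sits badly with the unequal change SDs. With a score SD of 20 (assumed), ρ = 1 − SD²/(2 × 20²) gives 0.80 in HPA and 0.53 in UC. Step 3 is therefore a guide to size, not a forecast.
- A reader might infer that mixing patient-rated and carer-rated POS-S-MS distorts the arm comparison. The documents do not support this: cognitive compromise, which largely decides who rates, is balanced by the minimisation, and a constant rater offset cancels in a change.

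**Conclusion.** The point holds as a matter of precision. The article restricts allocation on three factors, fully specifies only unadjusted tests, and states the mixed model without those factors or any handling of baseline. If the analysis were run unadjusted, intervals would be about 3 to 20% too wide for factor R² of 0.05 to 0.30, and not widened at 0. Ignoring baseline would cost about 5 to 13 power points for ρ of 0.7 to 0.3. The first range assumes near-perfect balance on the factors. The second assumes equal variances at baseline and follow-up and a common ρ. The two ranges should not be added, because baseline may already carry much of what the factors predict.

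The stronger reading, that the results would be biased or the false-positive rate inflated, does not follow: the error is conservative. It also does not follow that intervals must be too wide, since that depends on predictive strength that the article does not give. The change is worth making because it is nearly free in a small trial.

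**What to change.** In the Statistical analyses section, name one primary between-arm analysis for SEIQoL-DW and POS-S-MS: a linear mixed model of the three- and six-month scores with arm, categorical time and arm-by-time interaction. Adjust it for baseline score, EDSS band and center, and for POS-S-MS only, severe cognitive compromise. Make the t and Wilcoxon tests on these two outcomes descriptive or secondary.

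Do not add a separate term for respondent type, which nearly duplicates severe cognitive compromise. Do not set POS-S-MS to missing when a patient loses the ability to self-rate, because that would make missingness depend on outcome.

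The cost is wording plus five degrees of freedom for POS-S-MS (baseline 1, EDSS band 1, center 2, cognitive compromise 1) and four for SEIQoL-DW. No new data are needed, and the sample size can stay as it is.

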#### Withdrawals and loss to follow-up

Dyads can withdraw from the study at any time. The ‘intention-to-treat’ principle will apply for participants who withdraw or are lost to follow-up.

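### The only test stated for the continuous secondary and carer scales is a two-sample t or Wilcoxon test, less precise at month 6 than the mixed model already planned for the two primary scores

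*Protocol article*

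**What the plan says.** The Statistical analyses section begins with general methods for continuous data: "Between-group comparisons will employ either the two-sided unpaired" t test, or Wilcoxon's test if the data are not normal. It then turns to the two primary scores: "Longitudinal changes in SEIQoL-DW and POS-S-MS will be analyzed using linear mixed models for longitudinal data". On missing data it says: "For the primary intention-to-treat analyses, multiple imputation of missing values will employ Rubin’s approach".

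The section on withdrawals has no such limit. There the intention-to-treat "principle will apply for participants who withdraw or are lost to follow-up", whatever the outcome.

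The Secondary outcomes section lists Core-POS, EQ-5D, HADS, EDSS, FIM and costs for patients, and SF-36, EQ-5D, HADS and ZBI for carers. Table 2 shows that all of these except costs are taken by the examiner at baseline, three and six months, on the same schedule as the primary scores. No sentence extends the mixed model or the imputation to them.

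**The concern.** The article does state a method for continuous outcomes, so this is not a complaint about missing detail. On the ordinary reading, the secondary and carer scales get the general two-sample test, because the model is attached by name to two other scores.

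That is a weak choice for a scale measured three times. A test at month 6 needs a month-6 value. A dyad seen at baseline and month 3 but lost afterwards counts in the month-3 comparison and adds nothing at month 6 unless its value is imputed. The general sentence also makes no use of baseline as a covariate.

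All carer evidence is secondary, and the article itself calls 75 patients rather small for a phase II/III trial. Precision on these scales is scarce, and the protocol already contains a tool that would recover some of it.

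**Working it through.** **Stated figures.** The article gives none for secondary or carer outcomes. Its power figures for the primary scores reproduce with an unequal-variance t test (POS-S-MS, 41 and 21: 85.7% against 85% stated; SEIQoL-DW, 21 and 11: 80.1% against 80%), but they do not bear on this point.

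**Inputs from the article (Sample size).** 50 HPA and 25 UC; 20% loss, leaving 40 and 20.

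**Assumptions, not in the article.** SD of 1 at each visit, no true effect, and all loss between months 3 and 6. Two correlation patterns:
- A: 0.5 between every pair of visits.
- B: 0.5 (baseline and month 3), 0.7 (months 3 and 6), 0.4 (baseline and month 6).

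Let r be the baseline to month-6 correlation and R² the squared multiple correlation of month 6 on baseline and month 3.
- A: R² = (0.25 + 0.25 − 0.25)/0.75 = 0.333.
- B: R² = (0.49 + 0.16 − 0.28)/0.75 = 0.493.

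With all dyads, 1/50 + 1/25 = 0.060. With those remaining, 1/40 + 1/20 = 0.075.

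**Precision when loss is random (large-sample formulas).**

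| Analysis at month 6 | Variance | A: variance, SE | B: variance, SE |
|---|---|---|---|
| t test on change, observed dyads | 2(1 − r) × 0.075 | 0.0750, 0.274 | 0.0900, 0.300 |
| Same dyads, baseline as covariate | (1 − r²) × 0.075 | 0.0563, 0.237 | 0.0630, 0.251 |
| Baseline plus month 3 of lost dyads | (1 − R²) × 0.075 + (R² − r²) × 0.060 | 0.0550, 0.235 | 0.0580, 0.241 |

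A t test on the month-6 score itself has variance 0.075 and SE 0.274 under either pattern. Simulation at the actual sample sizes gives 0.27 to 0.30 SD for the t test on change and 0.24 to 0.25 SD for the likelihood model.

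Baseline adjustment supplies most of the gain:
- A: (0.0750 − 0.0563)/(0.0750 − 0.0550) = 94%.
- B: (0.0900 − 0.0630)/(0.0900 − 0.0580) = 84%.

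**How baseline enters matters.** If baseline is a response with a separate mean in each arm, the variance of the change contrast is (1 − R²) × 0.075 + [2(1 − r) − (1 − R²)] × 0.060.
- A: 0.0500 + 0.0200 = 0.0700, SE 0.265.
- B: 0.0380 + 0.0416 = 0.0796, SE 0.282.

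That is only slightly better than the t test.

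**Bias (simulation under no effect, t test on change in observed dyads).**
- Loss random, or working alike in both arms: about 0 SD.
- Loss depending on month-3 worsening in UC and random in HPA, 20% in each arm, log-odds 1.0 per SD: 0.08 to 0.15 SD.
- Same, log-odds 1.5: about 0.11 SD (A) and 0.19 SD (B), with 6.4% and 8.5% false positives.
- Same, log-odds 1.5, with 15% loss in HPA and 30% in UC: about 0.16 and 0.27 SD, with 8.6% and 13.1% false positives.
- 20% loss split evenly before and after month 3, early loss random, log-odds 0.5 to 1.5: 0.02 to 0.07 SD (A) and 0.04 to 0.11 SD (B).

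The likelihood model stayed within 0.01 SD of zero where it was run alongside. That is expected, because loss was simulated to depend only on observed values.

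**The case against.** The strongest reply is that this is a journal article. An analysis plan or full protocol, not shown, may extend the model to every scale. The general test sentence is not assigned to secondary outcomes, and the Sample size section uses a t test for the primary scores too. The phrase about primary intention-to-treat analyses could mean the main analyses of all outcomes. All of this is fair. It makes the point a matter of what the text fixes as it stands, not proof of what will be done.

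A reader might infer that the plan prescribes a completer analysis and discards lost dyads. The documents do not say so. Neither completers nor complete cases are mentioned, nothing says the model is for the primary scores only, and a dyad lost after month 3 still counts at month 3, the time point used for the sample size.

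A reader might also infer that the secondary comparisons are biased. That needs outcome-related loss that differs by arm. The article does not state this, and two of its features work against it: UC dyads get the same examiner visits and monthly calls, and they are offered HPA at the end of the study. The 20% loss is also attached to a three-month calculation, so it need not all fall after month 3.

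The last objection is that a linear model imposed on every scale would lose the provision for non-normal data. That stands, and the fix keeps the provision.

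**Conclusion.** The point holds as one of precision and consistency. As written, the only method stated for these three-visit secondary and carer scales is a two-sample test with no missing-data provision of its own. The article nevertheless applies intention-to-treat to all who withdraw or are lost, and already plans a better model for two scores.

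Under the assumed correlations and 20% loss, the formulas give standard errors 14% (0.235/0.274) to 20% (0.241/0.300) smaller than the t test on change. This requires baseline to be used for adjustment. Most of the gain comes from that, and a smaller part from the month-3 data of lost dyads. The 50 and 25 dyads apply to outcomes available in everyone. Patient EQ-5D and HADS are not taken in severe cognitive compromise, so their standard errors would be larger, but the ratio is the same if loss is similar.

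Bias is a possibility, not a finding. It is about zero if loss works alike in both arms, and 0.08 to 0.15 SD under a moderate UC-only mechanism that is purely an assumption.

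**What to change.** Extend the mixed-model sentence in Statistical analyses along these lines:

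*Longitudinal changes in SEIQoL-DW and POS-S-MS, in patient Core-POS, EQ-5D, HADS and FIM, and in carer SF-36, EQ-5D, HADS and ZBI will be analysed with the same linear mixed model, adjusting for baseline (as a covariate, or as a response with one mean common to both arms) and using all available assessments of randomized participants. For markedly non-normal scores, unpaired t or Wilcoxon tests will be reported as a sensitivity check.*

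EDSS and costs are left out, since a linear model is less natural for an ordinal grade or a skewed cost. If the analysis plan already says this, the article and the plan need only be aligned.

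The cost is a little more programming in the software already named and a check of residuals for each scale. A direct-likelihood analysis beside the imputation used for the primary analyses is a second technique, but both ordinarily rest on the same missing-at-random assumption. No new data or participants are needed.
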